#### Secondary outcome measures

##### Endurance shuttle walk test

The endurance shuttle walk test (ESWT) is a derivative of the ISWT. The patient walks between two shuttles along a 9-m track at a predefined speed, usually at 85% of the maximum speed derived from the ISWT. The test ends when the patient cannot continue because of symptoms (such as dyspnea or fatigue) or for a maximum of 20 min (test completion). The outcome of the ESWT is usually reported as time (minutes and seconds), although in some studies the distance completed (meters) has been used. Studies suggest that the ESWT is more sensitive to change after rehabilitation when compared to the 6MWT and ISWT [20, 21]. However, compared to our primary endpoint (ISWT), there is less evidence on using the ESWT and there are no reference values for the PPS population. The MCID for the ESWT has been demonstrated to be 174 to 279 s in COPD after pulmonary rehabilitation [22].

##### Modified MRC dyspnea scale

The mMRC scale is a widely used tool for evaluating the limitation of activities due to dyspnea. This short questionnaire consists of five statements describing the patient’s respiratory disability, ranging from 0 (“not troubled by breathlessness except on strenuous exercise”) to 4 (“too breathless to leave the house or breathless when dressing or undressing”). The MCID for the mMRC is 0.5 points [23].

##### The Shortness of Breath Questionnaire

The Shortness of Breath Questionnaire (SOBQ) is a patient-reported outcome measure which assesses subjective symptoms of dyspnea associated with activities of daily living (ADL). The SOBQ includes 24 items and each is scored on a scale from 0 (“not at all”) to 5 (“maximal/unable to do because of breathlessness”). Total scores range from 0 to 120 with a higher score indicating a higher degree of dyspnea.

##### Sensewear activity monitor

Daily physical activity is measured using a Sensewear activity monitor. The participants will wear the monitor for 1 week before and 1 week after the intervention period to investigate whether the intervention results in a change in daily physical activity or not by measuring the number of steps taken per day and time spent in different activity intensities. Sensewear is a multisensor activity monitor combining a triaxial accelerometer and is shown to be a reliable and valid tool for measuring physical activity in people with respiratory disease [24, 25].

##### EQ-5D-5L

The EQ-5D-5L has been developed by the Euroqol Group as a patient-reported outcome measure to assess generic health status and HRQoL in 5 different dimensions: mobility, self-care, usual activities, pain/discomfort, and anxiety/depression. Each dimension has 5 possible answers ranging from 1 to 5 with a higher score indicating worse possible state, and these scores can be aggregated to a utility score on a 0–1 scale using a tariff of preferences derived from a general population [26]. In addition, the patient subjectively scores their general HRQoL on a visual analogue scale from 0 (“worst imaginable state of health”) to 100 (“best imaginable state of health”).

##### Pulmonary Embolism Quality of Life Questionnaire

The Pulmonary Embolism Quality of Life Questionnaire (PEmb-QoL) is a disease-specific patient-reported outcome measure to assess HRQoL following PE [27]. The PEmb-QoL has 40 items over 6 domains, which assess symptom frequency, the time of day when complaints are at their worst, and the effect of pulmonary-specific symptoms on ADL and work-related problems. Scores for each domain range from 0 to 100 with the average score of all six domains being used to calculate the total score. A lower score indicates better HRQoL. The MCID for the PEmb-QoL is 15 points [28].

##### The Hospital Anxiety and Depression Scale

The Hospital Anxiety and Depression Scale (HADS) is a patient-reported outcome measure assessing symptoms of depression and anxiety. The HADS provides a total score with a 0–42 range with a higher score indicating that the patient is more symptomatic. Scores of ≥ 19 points indicate symptoms corresponding to cases of anxiety and depression, whilst scores between 15 and 18 points suggest possible symptoms of anxiety and depression. It is also possible to calculate a score for anxiety or depression only (range 0–21 points). Scores of ≥ 11 points indicate symptoms that can be compatible with anxiety/depression, and 8–10 points suggest possible symptoms of anxiety/depression. The MCID for the HADS has been suggested to be a reduction of 1.3 to 1.8 points in COPD patients undergoing pulmonary rehabilitation [29].

### Data collection

All outcome measures are completed at baseline and 12 and 36 weeks after inclusion (Figs. 1 and 2). In addition, a complete baseline evaluation is performed on all participants including a full history and medical examination, routine blood tests and biobanking (10 ml EDTA plasma, 10 ml citrated plasma, 10 ml serum, and 10 ml in paxgene), ventilation and perfusion scintigraphy, pulmonary function test (including spirometry, whole body plethysmography, carbon monoxide diffusing capacity of the lung), and transthoracic echocardiography. In addition, cardiac magnetic resonance imaging is performed on 50 participants without PPS and 50 participants with PPS before and after rehabilitation. Finally, patients will be asked to complete questions on self-reported physical activity and exercise habits.

**Fig. 1 Fig1:**
[figure not shown]
Study design

**Fig. 2 Fig2:**
[figure not shown]
Schedule of enrolment, interventions, and assessments

Data collected during the course of the research will be kept strictly confidential and will be stored in the secure research server at ØHT to which only the project investigators have access. Participants will be allocated an individual trial identification number and only de-identified data will be analyzed. The identification key will be stored in a separate file on the secure research server. Only the project investigators and the statistician analyzing the data will have access to the data set. Anonymized data may be shared with other researchers to enable international prospective meta-analyses.

### Data management and analysis

The results will be analyzed according to the intention-to-treat principle. Baseline characteristics will be described by mean and standard deviation, median and interquartile range, or number and proportions as appropriate. The effect of the intervention on the primary outcome (ISWT) will be assessed by comparing the change in exercise capacity after 12 weeks. The primary analysis based on the baseline data and data after 12 weeks will be conducted as a linear regression. The subsequent analysis, which will include data after 36 weeks, will have three measurements per individual to assess the short-term and long-term effect of the intervention and will therefore be analyzed using a linear mixed model. This variant of multiple linear regression allows for addressing such correlations as well as adjusting for possible confounders such as age, body mass index, sex, and treatment center. HRQoL, general activity, and the mMRC breathlessness scale will be compared between the 2 groups at 12 weeks using appropriate statistical tests depending on the normality of data. In addition, the model will also account for missing values. We will apply a post hoc sensitivity analysis to get an indication on potential bias caused by comparing potentially unequal groups with respect to time since PE at the time of inclusion. One way to achieve this is by the use of resampling techniques.

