### Sample size calculation

There is currently no data on the physical capacity of PPS patients as measured by ISWT. Therefore, in concurrence with the Danish study that was ongoing when we designed our protocol [30], we have based our sample size calculations on the mean improvement in ISWT previously reported in patients with cardiac and respiratory disease. Rolving et al. assumed that the achieved difference will be around 70 m, i.e., comparable to cardiac patients. Based on 6MWT results from a previous study in patients with PPS [6], patients walked between 413 and 480 m on 6MWT, which is closer to the cardiac population. Therefore, we assume a baseline ISWT for PE patients to be 390 m.

Based on calculations, our clinical experience, and on previous findings, an improvement of 60 m or more on the ISWT will be considered as being of clinical relevance. Given these assumptions, a required sample size to test for that effect size with a type 1 error of 5% and a type 2 error of 20%, 86 patients are needed in each study arm. By adding 10% attrition, the required sample size will be a total of 190 patients. No interim analysis will be performed.

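### The primary 12-week analysis is described as a regression on change in ISWT with no commitment to adjust for baseline ISWT; if it is unadjusted it is valid but less precise than it need be

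*Protocol article*

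**What the plan says.** The section Data management and analysis in the protocol article gives the primary contrast as follows: "The effect of the intervention on the primary outcome (ISWT) will be assessed by comparing the change in exercise capacity after 12 weeks". The method comes next: "The primary analysis based on the baseline data and data after 12 weeks will be conducted as a linear regression". Neither sentence names a covariate.

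The text then turns to the analysis that adds the 36-week data. With three ISWT values per person, this one is planned as a linear mixed model. Covariates are mentioned only after this, as a feature of that model: it allows for "adjusting for possible confounders such as age, body mass index, sex, and treatment center". The list is open-ended and does not include baseline ISWT.

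The Sample size calculation section sets the target: "an improvement of 60 m or more on the ISWT will be considered as being of clinical relevance". It continues "with a type 1 error of 5% and a type 2 error of 20%, 86 patients are needed in each study arm". It also gives an assumed starting level: "we assume a baseline ISWT for PE patients to be 390 m". That figure is a mean. No SD and no correlation between visits is given.

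**The concern.** Baseline ISWT is likely to be the strongest single predictor of 12-week ISWT, and every participant has it. Regressing change on arm alone fixes the baseline slope at 1. A baseline-adjusted regression estimates the slope from the data and so, apart from one degree of freedom, is never less precise. The article attaches the change contrast to the primary analysis and the named covariates to a different model, so the simplest reading of the primary model is the less efficient one.

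Two things are at stake. One is the width of the primary confidence interval, in a trial whose authors say they had no ISWT data in this population when they set the sample size. The other is analytic freedom. The mixed model is also meant to assess the short-term effect, so the 12-week difference may be estimated twice, once with no named covariates and once with a list that is still open.

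**Working it through.** **Inputs from the article.** Target difference 60 m; type 1 error 5% (taken as two-sided, since sidedness is not stated); power 80%; 86 per arm; 1:1 allocation.

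**Inputs assumed.** r, the correlation between baseline and 12-week ISWT, is taken from 0.5 to 0.9. The SDs at the two visits are taken as equal (s).

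**Step 1: reproduce 86 per arm.** The SD must be back-solved:

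SD = 60 / [(1.960 + 0.842) × √(2/86)] ≈ 140 m.

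Check: n = 2 × (1.960 + 0.842)² × 140² / 60² ≈ 85.5, which rounds up to 86. The article does not say whether this is the SD of change or of a single ISWT value.

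**Step 2: variance ratio.** The per-patient variance of change is 2(1−r)s². The residual variance after adjusting for baseline is (1−r²)s². Their ratio is (1−r²) / [2(1−r)] = (1+r)/2.

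Without the equal-SD assumption, the change-score variance exceeds the adjusted variance by (s₁ − r·s₂)², where s₁ and s₂ are the baseline and 12-week SDs. This is never negative.

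**Step 3: if 140 m is the SD of change.** The residual SD is 140 × √[(1+r)/2]. Power is by normal approximation at 86 per arm for 60 m, and is 80% without adjustment.

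| r (assumed) | Variance ratio | Residual SD (m) | n per arm for 80% power | Power at 86 per arm |
|---|---|---|---|---|
| 0.5 | 0.75 | 121 | 65 | 90% |
| 0.6 | 0.80 | 125 | 69 | 88% |
| 0.7 | 0.85 | 129 | 73 | 86% |
| 0.8 | 0.90 | 133 | 77 | 84% |
| 0.9 | 0.95 | 136 | 82 | 82% |

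**Step 4: if 140 m is instead the SD of a single ISWT.** The SD of change is 140 × √[2(1−r)] and the adjusted residual SD is 140 × √(1−r²). At r = 0.5 the results match the first row above (80% against 90%). At r = 0.7 the SDs are 108 m and 100 m, and power is about 95% without and 98% with adjustment. The variance ratio is unchanged, but the gain in power is small because power is already high.

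**Step 5: chance baseline difference.** Under the reading in Step 4, one standard error of the baseline difference between arms is 140 × √(2/86) ≈ 21.3 m. If the intervention arm starts that much higher, the change-score estimate is shifted by −(1−r) × 21.3 m: −10.7 m at r = 0.5, −6.4 m at r = 0.7 and −2.1 m at r = 0.9. Comparing 12-week values alone would shift it by +r × 21.3 m: +10.7, +14.9 and +19.2 m. Under the equal-SD linear model, baseline adjustment removes this shift.

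**The case against.** The strongest reply is that the text never calls the primary regression unadjusted. It says that the regression draws on baseline and 12-week data, which fits a model with baseline ISWT as a regressor. Speaking of change does not settle it, because once baseline is in the model, regressing change or the 12-week value gives the same treatment coefficient. A journal article also condenses its protocol, and the exact covariate set may sit in an analysis plan that is not shown. This stands: the loss is conditional on the model being unadjusted. What remains is that the article assigns a change contrast to the primary analysis and places named adjustment elsewhere without baseline ISWT, so the intended model should be settled.

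Three stronger readings are tempting, and the article does not support them.

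- A reader might infer that chance imbalance in baseline ISWT goes uncorrected. A change score subtracts baseline in full. What remains is an over-correction of (1−r) times the difference, in the opposite direction.
- A reader might infer bias or an inflated type 1 error. Under randomisation the change-score estimate is unbiased and its test is valid.
- A reader might infer that centre must be in the primary model because the second centre began recruiting 19 months after the first (January 2018 and August 2019, Trial status). A later start does not confound randomised arms. The Study design section describes blocks of 10 and states no stratification by centre, and any gain from including centre cannot be computed from the article.

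**Conclusion.** The point holds as an efficiency improvement, not as an error that must be corrected. The article does not commit the primary analysis to adjustment for baseline ISWT. If the model is change on arm alone, the primary result remains valid but its variance is larger than necessary: adjustment would lower it by 5% to 25% for r between 0.9 and 0.5, with equal variances.

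The increase in power from 80% to between 82% and 90% needs a further assumption, that the back-solved 140 m is the SD of change. If it is the SD of a single value, power at the higher correlations is already well above 80% and little is gained. Neither r nor the SD is in the article. If baseline ISWT is already intended as a regressor, no precision is lost and only the wording needs to be made explicit.

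**What to change.** Before outcomes are compared by arm, state the primary model: 12-week ISWT (or, equivalently, change in ISWT) regressed on arm and continuous baseline ISWT, with the adjusted mean difference and its 95% CI as the primary result. Say in the same sentence whether centre is included; it is a reasonable pre-specified covariate but an optional one.

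For the mixed model, replace the open list with a closed one fixed in advance, and use baseline ISWT in one role only. Either keep it as a response, with the arms constrained to a common baseline mean, or make it a covariate with only the 12- and 36-week values as responses. Adding it as a covariate while it is still one of the three responses would put it on both sides of the model.

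The cost is one or two sentences in the analysis plan. Baseline ISWT and centre are already recorded, so no new data and no change to the sample size are needed.

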## Methods and design

### Study design

A two-center RCT is being performed at the outpatient departments of Østfold Hospital Trust (ØHT) and Akershus University Hospital (AHUS) in Norway. Patients with PPS are 1:1 randomized into two arms, an intervention arm and a control arm, using sealed envelopes. The allocation sequence will be computer generated, and to ensure balanced recruitment during the study, this will be performed in blocks of 10. The allocation sequence will not be available to the person enrolling participants and the randomization code will be kept inside sealed opaque envelopes. The generation of the allocation sequence has been performed by the statistician at ØHT. The enrollment process and assignment of interventions will be performed by the PhD candidates.

In addition, a group of patients with no PPS following PE will be examined at baseline to compare patients with and without persistent dyspnea after PE in terms of exercise capacity, daily physical activity, dyspnea, and HRQoL.

The primary study objective is to explore the short-term changes in exercise capacity from baseline to 12 weeks after inclusion between groups as measured by the incremental shuttle walk test (ISWT). The secondary objectives are to explore the long-term effect of the rehabilitation program on exercise capacity 36 weeks after inclusion between groups (ISWT) as well as changes in exercise endurance (ESWT), subjective symptoms of dyspnea, daily physical activity levels, and HRQoL from baseline to 12 and 36 weeks after inclusion.

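### For HRQoL, daily activity and mMRC the plan names only a 12-week comparison by a normality-chosen test, although the objective is change from baseline to 12 and 36 weeks

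*Protocol article*

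**What the plan says.** All references are to the protocol article.

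- **Objective (Study design).** Besides the 36-week ISWT comparison, the secondary objectives are changes in ESWT and in "subjective symptoms of dyspnea, daily physical activity levels, and HRQoL from baseline to 12 and 36 weeks after inclusion".
- **Collection (Data collection).** "All outcome measures are completed at baseline and 12 and 36 weeks after inclusion". The Methods part of the abstract likewise lists these outcomes among those on which the arms are compared, from assessments at all three visits.
- **Analysis (Data management and analysis).** For ISWT, "The primary analysis based on the baseline data and data after 12 weeks will be conducted as a linear regression". A later analysis that adds the 36-week data "will have three measurements per individual to assess the short-term and long-term effect of the intervention" and uses a linear mixed model. The next sentence on outcomes says that HRQoL, general activity and mMRC "will be compared between the 2 groups at 12 weeks using appropriate statistical tests depending on the normality of data". After it comes a statement that the model will deal with missing values.
- **Reference values.** "The MCID for the mMRC is 0.5 points". The PEmb-QoL section gives an MCID of 15 points.
- **Activity monitor (Sensewear activity monitor).** Wear is described for one week before and one week after the intervention period. No 36-week wear is mentioned there.

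**The concern.** This goes beyond a detail left to a later document. The article states a method for three secondary outcomes, and that method does not match its own objective. The objective has two time points and is framed as change. The stated analysis has one time point and mentions neither change nor baseline. Dyspnea and HRQoL also stand in the primary hypothesis next to exercise capacity, so they are not peripheral.

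The test rule is a separate problem. A t-type test addresses a difference in means, while a rank test addresses a tendency towards higher or lower values. If a look at the distribution decides between them, the quantity reported is not fixed in advance and may differ from one outcome to the next. A rank test alone gives no estimate in points to hold against 0.5 for mMRC or 15 for PEmb-QoL. For mMRC, with five ordered categories, normality is not a useful criterion in any case.

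At stake are a stated 36-week objective with no explicitly named analysis, some avoidable loss of precision at 12 weeks, and results that may not be readable against the plan's own thresholds.

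**Working it through.** **1. The texts side by side**

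| Outcome | Objective | Collected | Analysis named |
|---|---|---|---|
| ISWT | 12 weeks (primary), 36 weeks (secondary) | 0, 12, 36 | Linear regression at 12 weeks; then mixed model with three measurements |
| HRQoL | Change to 12 and 36 weeks | 0, 12, 36 | 12-week comparison, test by normality |
| mMRC (dyspnea) | Change to 12 and 36 weeks | 0, 12, 36 | 12-week comparison, test by normality |
| Daily activity | Change to 12 and 36 weeks | 0, 12, 36 by Data collection; before and after the intervention by the Sensewear section | 12-week comparison, test by normality |

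The mixed-model sentence follows directly on the ISWT sentences and names no secondary outcome.

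**2. The plan's own figure**

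The only sample size is for ISWT: 86 per arm, for 60 m, 5% type 1 and 20% type 2 error. No SD is given, so it can only be solved backwards. With a two-sided test, n = 2·SD²·(1.960 + 0.842)²/60², so SD = 60·√(86/2)/2.802 ≈ 140 m. The implied standardized difference is 60/140.4 = 0.427. For attrition, 172 × 1.10 = 189.2, rounded up to 190. None of this is in dispute. The 0.427 serves only as a yardstick below, because no SD or power is given for any secondary outcome.

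**3. What baseline adjustment is worth**

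Assume equal variance σ² at baseline and follow-up and a correlation r between them. The documents give no r. Per-patient variances are:

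- raw 12-week value: σ²
- change score: 2(1 − r)σ²
- ANCOVA: (1 − r²)σ²

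Hence ANCOVA/raw = 1 − r², and ANCOVA/change = (1 − r²)/[2(1 − r)] = (1 + r)/2. Power is Φ(0.427·√(86/2)/√f − 1.960), where f is the variance factor and there are 86 per arm.

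| r (assumed) | ANCOVA/raw | ANCOVA/change | Power raw | Power change | Power ANCOVA |
|---|---|---|---|---|---|
| 0.3 | 0.91 | 0.65 | 80.0% | 65.8% | 83.6% |
| 0.5 | 0.75 | 0.75 | 80.0% | 80.0% | 89.9% |
| 0.6 | 0.64 | 0.80 | 80.0% | 87.9% | 93.8% |
| 0.7 | 0.51 | 0.85 | 80.0% | 95.1% | 97.5% |
| 0.8 | 0.36 | 0.90 | 80.0% | 99.3% | 99.7% |

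At r = 0.7, ANCOVA is worth 1/0.51 = 1.96 times the sample against raw values, but only 1/0.85 = 1.18 times against change scores. It is the most precise of the three at every r shown.

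**The case against.** The strongest reply is that much of the worry reads silence as a statement, and on several points that is right.

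- **Baseline ignored?** A reader might infer that the 12-week tests are unadjusted. The text does not say so. Study design speaks of changes, and the ISWT effect is assessed by comparing change, so change scores are a natural reading. The precision gain then shrinks to (1 + r)/2. Randomization also makes even a raw 12-week comparison unbiased.
- **Only 12 weeks, and nothing at 36?** The word only does not appear. The mixed-model sentence names no outcome, and the missing-values sentence after the secondary outcomes refers to a model. A mixed model for these outcomes cannot be ruled out, although it is not stated.
- **Patients with missing values dropped?** That same sentence speaks against it.
- **ESWT, SOBQ and HADS not analyzed?** They are not named in the analysis section, but a condensed article may leave them to the analysis plan. HADS is not among the stated objectives either.
- **mMRC.** A normality rule would probably lead to a rank test, which is valid for ordinal data. An ordinal model gives an odds ratio, which is no more comparable with a 0.5-point MCID than a rank test is.

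What stands is the mismatch between objective and named analysis for three outcomes, and the normality-based choice, which is written outright. At best the section is ambiguous about 36 weeks, and that needs correcting too.

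**Conclusion.** The point holds for HRQoL, daily activity and mMRC. The one analysis named for them does not cover the stated objective, and the test rule leaves the reported quantity to the data. Two stronger claims are not supported: that secondary outcomes in general lack a 36-week analysis (the mixed model covers 36-week ISWT), and that baseline is known to be ignored.

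The size rests on an assumed r and on equal variances over time. For r from 0.5 to 0.7, baseline adjustment brings the variance to 0.75 to 0.51 of that of a raw 12-week comparison, or to 0.75 to 0.85 of that of a change-score comparison. Which range applies cannot be told from the article. This should be fixed, but it does not threaten the trial: the ISWT analysis, sample size and primary conclusion are unaffected.

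**What to change.** 1. Replace the normality-dependent test for continuous secondary outcomes with the linear mixed model already planned, adjusted for the baseline value of the outcome. Report the arm difference with 95% CI at 12 and at 36 weeks, with robust or bootstrap errors where data are skewed.
2. For mMRC, use an ordinal model adjusted for baseline mMRC. If the result is to be judged against the 0.5-point MCID, also report the mean difference with CI.
3. Reconcile the Sensewear section with Data collection and Study design on whether activity is measured at 36 weeks. If it is not, limit the activity analysis, and its objective, to 12 weeks.
4. Say which model the missing-values sentence refers to.

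The cost is wording and a little extra analysis. No new data are needed, provided that activity is analyzed only at the times when it is measured. The change should be made before unblinded results are seen.
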